## 167 I. RATIONALE OF THE STUDY AND SCIENTIFIC JUSTIFICATION

### 168 I.1. Management of early stage cancers of the oral cavity 169 and oropharynx

170 Early stage cancers of the oral cavity and oropharynx are in the majority of cases squamous  
171 cell carcinomas. The main risk factors are tobacco, alcohol and HPV infection. Their impact is  
172 growing (1). Their care is multidisciplinary. In localized forms, surgery is generally the first-line  
173 treatment when it is possible (2). Surgical exploration of the cervical lymph nodes is most often  
174 performed either by dissection or sentinel lymph node (3–5). Negative resection margins (>5 mm)  
175 are recommended (6,7). In case of positive margins, new surgery should be proposed when possible.  
176 When this is not retained, post-operative radiotherapy is indicated (8–11). This post-operative  
177 radiotherapy may be limited to the tumour bed in the case of pT1-2 and negative cervical exploration  
178 (or if only one lymph node is affected without capsular rupture in the case of a carcinological  
179 dissection) (11,12). Two types of radiotherapy are used when irradiation of the operating bed alone  
180 is indicated: brachytherapy or normofractionated external beam radiotherapy (recommended in  
181 intensity-modulated conformal radiotherapy [IMRT]).

### 182 I.2. Postoperative radiotherapy for early stage cancers of 183 the oral cavity and oropharynx

#### 184 I.2.1 Postoperative brachytherapy

185 Brachytherapy is a highly conformal technique that allows a high dose to be delivered, in a  
186 small volume, in a short time (13–15). However, it is not always feasible: involvement of the gum or  
187 retromolar trigon, a distance of less than 5 mm from the gum, infiltration of the intermaxillary  
188 commissure, or extension to the parapharynx, to the cavum for an oropharyngeal tumor, to the union  
189 of the three folds or to the larynx. In addition, brachytherapy requires highly trained teams,  
190 hospitalization of the patient, general anesthesia, and adapted infrastructure.

191 Goineau et al. (16) reported the results of 112 patients treated with postoperative low-dose-  
192 rate (LDR) interstitial brachytherapy by Ir for squamous cell carcinomas of the mobile tongue. The  
193 local control rate at 2 years was 79% and at 5 years was 76%. The overall survival rate at 2 years was  
194 72% and at 5 years was 56%. 22% of patients experienced radionecrosis requiring surgery. 8% of  
195 patients presented with chronic pain requiring the use of morphine. These results were similar to those  
196 of other smaller retrospective studies (13,17,18). In the study by Lapeyre et al. (18) the local control  
197 rate was 81% and the 5-year overall survival rate was 70% for patients with T1/T2-N0 tumors. Strnad

et al. (19) reported the results of the largest brachytherapy study with 385 patients. Patients were treated with pulsed flow brachytherapy (PDR). Brachytherapy was postoperative in 85% of cases. The local control and overall 5-year survival rates were 85% and 69% respectively. The rates of severe late toxicity of mucosal ulceration and osteoradionecrosis were 10 and 5%, respectively.

### ***1.2.2 Postoperative intensity-modulated radiotherapy (IMRT)***

Postoperative normofractional IMRT is, along with brachytherapy, the second option of irradiation but mobilizes the patient for 6 to 7 weeks (20–24). No randomised trials compared the carcinologic outcomes and toxicity profiles of postoperative brachytherapy with postoperative IMRT in localised cancers of the oropharynx and oral cavity. Studies reporting the results of postoperative normofractional IMRT in cancers of the oropharynx and oral cavity often group together localized and locally advanced cancers. Collan et al. (23) reported a grade  $\geq 3$  acute mucositis rate of 25% in 102 patients. For late toxicities, 5% of patients required a permanent feeding tube and 30% had a grade 2 xerostomia. Geretschlger et al. (22) reported the results of 53 patients treated for oral cancers. They reported a rate of grade 3 acute mucositis of 36%, grade 2 late xerostomia of 6%, osteoradionecrosis of 4%, grade 3 mucosal ulceration of 2% and 9% permanent feeding tube. Other studies have reported similar toxicity profiles (20,21,24). Overall, rates of severe acute mucositis and permanent feeding tube were reported in 11-36% and 5-10% respectively. Rates of severe late mucosal ulceration (grades 3-4) ranged from 2 to 4% and osteoradionecrosis from 0 to 5% (20–24).

### ***1.1.3 Hypofractionated stereotactic radiotherapy in head and neck cancers***

Hypofractionated stereotactic radiotherapy delivers an ablative dose of radiation to extracranial tumors in one or more fractions using advanced planning and treatment techniques (25–28). This technique has the advantage of offering a highly conformational treatment, in a limited number of fractions, with a strong dose gradient leading to limited irradiation of the surrounding healthy tissues (28). The use of this technique is currently possible due to the rapid expansion of the French stereotactic technical park, but needs to be well supervised (27,29–35). Stereotactic radiotherapy in head and neck cancers has mainly been studied in cases of re-irradiation or boost.

#### ***• Stereotactic radiotherapy in re-irradiation***

Stereotactic radiotherapy studies in re-irradiation of head and neck cancers give us information about the acute toxicity of this technique. Information on late toxicity and efficacy would be difficult to compare.

228 Heron et al. (31) reported the results of a Phase 1 dose-escalation study of stereotactic  
 229 radiotherapy in case of re-irradiation for recurrences of squamous cell carcinomas of the head and  
 230 neck. A total of 25 patients received doses ranging from 5Gy to 8.8Gy per fraction, in 5 fractions over  
 231 2 weeks. No Grade  $\geq 3$  limiting dose toxicity has been reported. The same team reported its results  
 232 on 96 patients (33), showed a dose-response effect with a higher local control rate for tumors  
 233 receiving higher doses. An update of these results has been published (35). This study included 132  
 234 patients treated with a median dose of 44Gy (35-50Gy). They found a higher incidence of acute (but  
 235 not late) toxicity for patients with a tumor volume of more than 25 cm^3.

236 Two non-randomized phase II studies reported the results of stereotactic radiotherapy with  
 237 concomitant cetuximab in the setting of recurrence or second cancer in the irradiated territory, which  
 238 were not operable. The first study by Lartigau et al. (29) included 56 patients treated with a dose of  
 239 36 Gy in 6 fractions over 2 weeks on Cyberknife. In terms of acute toxicity, grade  $\geq 3$  mucositis was  
 240 found in 4/56 patients and grade  $\geq 3$  dysphagia in 3/56 patients. The second study by Vargo et al. (36)  
 241 included 48 patients treated with a dose of 40-44 Gy in 5 fractions over 1-2 weeks with different types  
 242 of accelerators (Cyberknife, Trilogy or Truebeam). 3/48 patients experienced at least one type of  
 243 grade 3 acute toxicity: 1 patient had mucositis and epidermatitis, 1 patient had dysphagia and the third  
 244 had epidermatitis. There was no significant difference in terms of carcinologic results, toxicity or  
 245 feasibility between the different types of accelerators. In these two studies by Lartigau et al.(29) and  
 246 Vargo et al.(36), the authors concluded that this treatment was feasible with acceptable toxicities.

247 Another study by Vargo et al.(34) studied 28 patients with margin at risk treated  
 248 postoperatively with stereotactic radiotherapy in irradiated territory at a dose of 40 Gy in 5 fractions.  
 249 There was 39% oral and oropharyngeal cavity in this study. No grade 3 acute toxicity was observed.  
 250 In another study by Vargo et al. (30) of 12 inoperable elderly patients with stage III-IV tumors in the  
 251 non-irradiated territory, treated with stereotactic radiotherapy alone (44 Gy in 12 fractions), grade 3  
 252 acute toxicity was observed in 1/12 dysphagia patients and grade 3 late toxicity was observed in 1/12  
 253 patients also with mucositis type.

254

255 • **Stereotactic radiotherapy in boost**

256 Hypofractionated stereotactic radiotherapy in head and neck cancers has also been evaluated as a  
 257 boost after initial normofractionated IMRT. Al-Mamgani et al. (37) studied stereotactic radiotherapy  
 258 as a therapeutic option for boosting oropharyngeal cancers not eligible for brachytherapy. 51 patients  
 259 received a 3 x 5.5Gy boost after an IMRT of 46Gy on the primary tumor and neck. The authors  
 260 reported that overall tolerability was good, there were no discontinuations of treatment for toxicity,  
 261 and no grade 4 or 5 acute or late toxicities. The cumulative incidence of Grade  $\geq 2$  late toxicity was

262 28%. Among the recurrence-free patients at 2 years (n=20), there was only 1 patient with a feeding  
 263 tube and 2 patients with grade 3 xerostomia. This same team reported its efficacy and toxicity results  
 264 of two different boost modalities for T1-T2 squamous cell carcinomas of the oropharynx:  
 265 hypofractionated stereotactic radiotherapy or brachytherapy (38). The 3-year local control rates for  
 266 stereotactic radiotherapy were 97% and 94% respectively (p=0.33). The 3-year recurrence-free  
 267 survival rates were 92% and 86% (p=0.15) respectively and the overall survival rates were 81% and  
 268 83% (p=0.82). The feeding tube rates were 17% and 20% respectively (p=0.47). The rates of late  
 269 dysphagia grade  $\geq 2$  were 11% and 8% (p=0.34) and xerostomia of 16% and 12% (p=0.28),  
 270 respectively. The authors concluded that due to the heavy logistics required for implantation, the need  
 271 for a trained team and the risks of general anesthesia and perioperative complications, stereotactic  
 272 radiotherapy seemed to be the optimal option for boosting localized oropharyngeal cancers compared  
 273 to brachytherapy.

### 274 **I.3. Hypofractionated stereotactic radiotherapy of the** 275 **operating bed in early stage cancers of the oral cavity** 276 **and oropharynx with high risk margin**

277 In our study, we hypothesize that the safety and efficacy profile of stereotactic radiotherapy of  
 278 the operative bed in localized cancers of the oral cavity and oropharynx with risk margins will be  
 279 similar to that of other radiotherapy techniques: brachytherapy or normofractionated IMRT.  
 280 Stereotactic radiotherapy could become the third therapeutic option in this indication. The use of  
 281 stereotactic radiotherapy of the operating room for localized cancers of the oropharynx and oral cavity  
 282 with risk margins would have several advantages:

- 283 • Highly conformal technique such as brachytherapy
- 284 • Fewer contraindications than brachytherapy due to tumor extension and/or implantation  
 285 difficulties
- 286 • Carrying out the treatment on an outpatient basis, without hospitalization or general  
 287 anesthesia, unlike brachytherapy
- 288 • Short spreading: 6 fractions over 2 weeks vs. 30-33 fractions over 6-7 weeks for fractional  
 289 IMRT.

290 The post-operative use of hypofractionated radiotherapy (excluding re-irradiation) has already  
 291 been reported in ENT cancers, particularly in the context of mucosal melanomas (39–41). Most of  
 292 these studies did not use stereotactic irradiation. Wu et al. (41) reported in 2010 their experience on  
 293 27 patients, 10 of whom were treated at a dose of 5x6Gy over 2 weeks and 8 patients at a dose of

294 3x7-8Gy over 3 weeks. In this study, 3/27 patients experienced Grade 3 acute toxicity (2 epidermatitis  
295 and 1 mucositis) and no patients had Grade 4 acute toxicity. With a median follow-up of almost 4  
296 years, no grade  $\geq 3$  toxicity was reported.

297 In total, a dose of 36Gy in 6 fractions over 2 weeks seems to be a good compromise postoperatively  
298 in terms of benefit/risk. To determine the effective biological doses (BEDs), we used the following  
299 formula to take into account the tumor doubling time (Tp), the spread of radiotherapy and the cell  
300 repopulation coefficient (Tk) (42,43):

$$\text{BED} = nd \left( 1 + \frac{d}{\alpha/\beta} \right) - \frac{\text{Ln}2(T - T_k)}{\alpha T_p}$$

301  
302 With this model, we obtain for the tumor bed a BED10 of 64.2 Gy for a Tk at 21 days (equivalent to  
303 the BED10 of 60 Gy in 30 fractions); a BED10 of 54.4 Gy for acute side effects (equivalent to the  
304 BED10 of 74 Gy in 37 fractions); a BED3 of 108Gy for late side effects (equivalent to the BED3 of  
305 66 Gy in 33 fractions).

#### 306 **I.4. Statement of Assumptions and Objectives**

307 In this study, we hypothesize that the safety and efficacy profile of stereotactic radiotherapy  
308 of the operative bed in localized cancers of the oral cavity and oropharynx with risk margins will be  
309 similar to that of other radiotherapy techniques: brachytherapy or normofractionated IMRT.  
310 Stereotactic radiotherapy could become the third therapeutic option to treat localized cancers of the  
311 oral cavity and oropharynx with risk margin.

312 The main objective of the study will be to evaluate the late toxicity of stereotactic radiotherapy  
313 of the operating bed of localized cancers of the oral cavity operated with risk margins.

#### 314 **I.5. Benefit-risk ratio**

315 The expected benefits for the patient are:

- 316 • Shorter treatment than normofractionated IMRT: 2 weeks vs. 6-7 weeks
- 317 • Treatment less severe than brachytherapy: no hospitalization or general anesthesia
- 318 • Maintaining a good quality of life during treatment
- 319 • Efficacy and tolerability profiles at least equivalent to standard treatments
- 320 • Good accessibility to innovative treatment throughout the country

321 The expected benefits in terms of public health are:

- 322 • Prospective evaluation of an innovative treatment

- Standardization and optimization of stereotactic radiotherapy in head and neck cancers (supported by GORTEC's high-level quality control) leading to improved professional practices
- Development of an innovative treatment with an expected cost-effectiveness ratio

The foreseeable and known risks are the same as for standard treatments in this indication, which are brachytherapy and normofractional IMRT.

The evaluation of acute and late toxicities is one of the secondary objectives of the study. The toxicity profile will be assessed using the NCI-CTCAE v.4.03 scale. Any toxicity, and its potential attributable to stereotactic radiation therapy, will be graded and recorded by the investigator. Particular attention will be paid to the evaluation of the following toxicities possibly related to stereotaxy: mucositis, dysphagia, xerostomia, mandibular osteonecrosis, soft tissue necrosis, epidermatitis and fibrosis.

## I.6. Expected benefits

In the event that this study confirms that the safety and efficacy profile of stereotactic radiotherapy of the operating bed in localized cancers of the oral cavity and oropharynx with risk margins is similar to that of other radiotherapy techniques (brachytherapy or IMRT), stereotactic radiotherapy could become the third therapeutic option to treat localized cancers of the oral cavity and oropharynx with margin at risk.

## II. OBJECTIVES OF THE STUDY

### II.1. Main objective

The main objective is to evaluate the late toxicity of stereotactic radiotherapy of the operating bed of localized cancers of the oral cavity operated with risk margins.

### II.2. Secondary Objectives

The secondary objectives will be to evaluate at 2 years:

- The local control rate
- The locoregional control rate
- Recurrence-free survival
- Overall survival
- Patients' quality of life
- Nutritional impact

- Acute toxicity (grade  $\geq 3$  occurring during treatment and up to 3 months after the end of treatment)
- Determining Predictors of Toxicity

#### Exploratory objective:

- to study the dosimetric impact of the addition of non-coplanar arcs to the Novalis accelerator-modulated volumetric arc therapy technique, and to study the dose-toxicity relationship on the first 10 patients treated with this technique

### III. STUDY DESCRIPTION

This is a Category I, non-drug, Phase II, multicentre, national, non-randomized, open-label human research with the primary outcome of which is the rate of severe late toxicity (grade  $\geq 3$ ).

### IV. RESEARCH DESIGN

#### IV.1. Primary endpoint

**Rate of patients with late toxicity at 2 years grade  $\geq 3$**  according to the NCI - CTCAE V4.03 classification in connection with hypofractionated stereotactic radiotherapy, i.e. grade  $\geq 3$  toxicities occurring beyond 3 months after the end of stereotactic radiotherapy.

#### IV.2. Secondary endpoints

- **Local control at 2 years.** Will be considered as an event: local recurrence (T) documented in the area of the operating bed. The diagnosis of local recurrence requires histological confirmation.
- **Locoregional control at 2 years.** The following are considered to be events: local recurrence (T) and/or lymph node recurrence (N), i.e. ipsilateral or contralateral cervical positive lymphadenopathy(es). The diagnosis of regional recurrence requires confirmation by imaging and/or histologic.
- **Grade  $\geq 3$  acute toxicity** (toxicities occurring during treatment up to  $\leq 3$  months after the end of treatment) in connection with hypofractionated stereotactic radiotherapy, according to the NCI classification - CTCAE V4.03
- **2-year recurrence-free survival (RSS):** defined as the time interval between the date of inclusion and the date of the first cancer event (local recurrence, regional recurrence, distant metastasis) or death from any cause.

- 385 • **2-year overall survival (OS):** defined as the time interval between the date of inclusion and
- 386 the date of death from any cause.
- 387 • **Quality of Life (QoL):** according to the EORTC QLQ-C30 and EORTC-H&N35
- 388 questionnaires
- 389 • **Nutritional impact,** assessed by patient weight and feeding tube use.
- 390 • **Predictive factors of toxicity at 2 years :** clinical and/or dosimetric factors associated with
- 391 late severe toxicity.

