## VI.2. Recruitment procedures

Patients will be screened in a Multidisciplinary Consultation Meeting (RCP) and those who are potentially eligible for the study (indication of irradiation of the operating bed) will be seen in consultation by a radiotherapist and/or a surgeon, who will offer them to participate in the trial. Patients who meet the inclusion criteria without non-inclusion criteria, and who have signed informed consent will be eligible to participate in this trial. Inclusion is done via the electronic CRF and must be performed before the start of stereotactic radiotherapy. The included patients will be treated according to the modalities provided for in the trial.

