### 535 ***VI.5.1 Assessment during immediate follow-up visits***

#### 536 **Follow-up visit at 14±3 days after the last stereotactic radiation therapy session**

- 537 • Clinical examination including weight  
 538 • Assessment of general condition according to WHO status  
 539 • Tumor bed examination (clinical +/- nasofibroscopy)  
 540 • Examination of the mouth, throat and neck

- 541 • Type of feed (Solid, liquid, mixed...)
- 542 • Acute toxicity assessments according to NCI-CTCAE v.4.03
- 543 • Collection of concomitant treatments

544

545 **Follow-up visit at 30±5 days after the last stereotactic radiotherapy session**

- 546 • Clinical examination including weight
- 547 • Assessment of general condition according to WHO status
- 548 • Tumor bed examination (clinical +/- nasofibroscopy)
- 549 • Examination of the mouth, throat and neck
- 550 • Type of feed (solid, liquid, mixed, etc.)
- 551 • Acute toxicity assessments according to NCI-CTCAE v.4.03
- 552 • Collection of concomitant treatments
- 553 • EORTC QLQ-C30 and H&N35 Questionnaire

554

555 **Follow-up at 3 months ±10 days after the last stereotactic radiation therapy session**

- 556 • Clinical examination including weight
- 557 • Assessment of general condition according to WHO status
- 558 • Tumor bed examination (clinical +/- nasofibroscopy)
- 559 • Examination of the mouth, throat and neck
- 560 • Type of feed (solid, liquid, mixed, etc.)
- 561 • Acute toxicity assessments according to NCI-CTCAE v.4.03
- 562 • Carcinologic evaluation:
  - 563 ❖ CT scan or cervicofacial MRI (*The choice between MRI and CT is left to the*
  - 564 *discretion of the investigator but follow-ups must be carried out with the same*
  - 565 *technique)*
  - 566 ❖ Chest CT scan (*The use of PET-FDG is left to the choice of the investigators in each*
  - 567 *center if it is medically indicated)*

568

569

570 **VI.5.2 Assessment during long-term monitoring visits**

571 These visits will take place every **3 months±10 days for up to 2 years** after stereotactic radiotherapy

572 and include:

- 573 • Clinical examination including weight
- 574 • Assessment of general condition according to WHO status
- 575 • Tumor bed examination (clinical +/- nasofibroscopy)

- 576 • Examination of the mouth, throat and neck
- 577 • Type of feed (solid, liquid, mixed, etc.)
- 578 • Late toxicity assessments according to NCI-CTCAE v.4.03
- 579 • Carcinologic assessment at **12 months and 24 months**

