## VI.8. Effectiveness evaluation

### VI.7.1 Locoregional control

626 Evaluation of the tumor bed (clinical +/- nasofibroscopy) and cervical lymph nodes will be  
627 performed in accordance with the table of investigations and evaluations (see Table 1).

628 Evaluation by imaging (+/- panendoscopy) will be repeated as soon as appropriate in case of clinical  
629 doubt about tumor recurrence. Imaging evaluation will be systematic at 3 months, 1 year and 2 years  
630 after the end of radiotherapy.

631

632 • **Local recurrence**

633 Recurrence will be considered local if documented in the operative bed area. The diagnosis of local  
634 recurrence requires histological documentation. The date of recurrence will therefore be equal to the  
635 date of the biopsy that allowed histological confirmation.

636 • **Regional recidivism**

637 Recurrence will be considered regional if it occurs in the form of positive lymphadenopathy at the  
638 ipsilateral or contralateral cervical level

639 The diagnosis of a regional recurrence requires confirmation by imaging (CT scan and/or MRI and/or  
640 PET-FDG) and/or histological. The date of regional recurrence will be the date of the CT scan or  
641 MRI or PET – FDG highlighting the progression or the date of the biopsy in case of histological  
642 confirmation.

643 If histological confirmation of regional recurrence cannot be obtained, the diagnosis may be made  
644 based on the investigator's judgment.

645 **VI.7.2 Remote Recidivism**

646 The remote diagnosis of recurrence will be performed when one of the following criteria is met:

- 647 • Clear radiological evidence of distant metastasis on imaging (CT or MRI or PET – FDG)
- 648 • Positive biopsy (in case of radiological doubt or clinically suspected recurrence such as skin  
649 metastasis or palpable mass)

650 The date of distant recurrence will be the date of the CT scan or MRI or PET – FDG highlighting the  
651 metastases or the date of the biopsy in case of histological confirmation.

652 If histological confirmation of distant recurrence cannot be obtained, the diagnosis may be made  
653 based on the investigator's judgment.

654

655 **VI.7.3 Second cancer**

656 The diagnosis of a second cancer requires histopathological evidence of a new tumor mass outside  
657 the operative bed area, which is not consistent with the diagnosis of local recurrence or regional lymph  
658 node recurrence.

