#### 662 **VI.7.4 2-year recurrence-free survival (SSR)**

663 SSR is defined as the time interval between the date of inclusion and the date of the first carcinologic  
664 event (local recurrence, lymph node recurrence, distant recurrence(s)) or death from any cause.

665 Patients alive without disease recurrence (as defined above) will be censored on the date of the last  
666 follow-up visit.

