### 906 IX.2. Data analysis: general

907 Patients will be described and compared between groups at baseline according to the following  
908 variables:

- 909 • Compliance with eligibility criteria
- 910 • Epidemiological characteristics
- 911 • Clinical and treatment characteristics.

912 A description of the deviations from the protocol, the patients distributed according to these  
 913 deviations and the causes of abandonment will also be carried out. The number of patients included  
 914 and the curve of inclusions will be presented by groups.

915 Continuous variables will be presented as a mean and standard deviation, subject to the normality of  
 916 their distribution (Shapiro-Wilk test if necessary). In case of non-normality, they will be presented in  
 917 the form of median, quartiles and extreme values. The qualitative variables will be expressed in terms  
 918 of numbers and associated percentages. 95% confidence intervals (95% CI) will be reported. For each  
 919 variable, the number of missing data will be specified. Graphical representations will be associated  
 920 with these analyses as much as possible.

921 The estimate of the theoretical follow-up time will be the time difference between the date of inclusion  
 922 and the date of the database freeze. The follow-up will also be estimated according to the reverse  
 923 Kaplan Meier method for the observed follow-up. The parameters related to the time to events (SSR,  
 924 OS...) as well as the time to deterioration of quality of life (scores) will be estimated according to the  
 925 Kaplan-Meier method and described with a median confidence interval and rates at defined periods.  
 926 Patients without specific events at the time of study termination (baseline freeze of study data) will  
 927 be censored, for the "time to events" criteria, as of the date of the last update. Possible comparisons  
 928 between independent groups will consider the log-rank test (univariate analysis) and the Cox model  
 929 (multivariate analysis).

930 Tests will be bilateral, and a  $p < 0.05$  value will be considered statistically significant. As this trial  
 931 is exploratory, the adjustment of the risk of error of the first kind will not be proposed systematically,  
 932 but on a case-by-case basis in view of clinical and not only statistical considerations (48).

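### 2-year recurrence-free survival is counted from inclusion but the 24-month scan from the end of radiotherapy, so recurrences first found at that scan mostly fall outside the 2-year rate

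*Protocol*

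**What the plan says.** **Clock for RFS.** Section IV.2 has RFS "defined as the time interval between the date of inclusion and the date of the first cancer event", with death from any cause also counting. Section VI.7.4 repeats the origin: "SSR is defined as the time interval between the date of inclusion and the date of the first carcinologic" event. Inclusion is made in the electronic CRF and "must be performed before the start of stereotactic radiotherapy" (VI.2). Table 1 places the inclusion visit on days J-28 to J-1.

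**Clock for visits and scans.** Long-term visits take place every 3 "months±10 days for up to 2 years" after stereotactic radiotherapy (VI.5.2). Section VI.7.1 states: "Imaging evaluation will be systematic at 3 months, 1 year and 2 years" "after the end of radiotherapy". The row header of Table 1 instead counts from the start of radiotherapy.

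**Dating of events.** A local recurrence takes the "date of the biopsy that allowed histological confirmation". Regional and distant recurrences take the date of the scan, or of the biopsy when there is one (VI.7.1, VI.7.2).

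**Estimation.** Section IX.2 uses Kaplan-Meier and reports "rates at defined periods". Section II.2 sets the evaluation of RFS at 2 years. Nothing assigns the 24-month assessment to the 2-year time point, and no landmark window is given.

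**The concern.** The protocol calls two different moments 2 years: two years from inclusion for RFS, and two years from the end of radiotherapy for the last examination and scan. The second comes later, because it adds the wait before treatment and the treatment itself. A recurrence first seen at the last assessment then carries a date beyond the point at which the RFS curve is read, and the patient counts as event-free at 2 years.

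The error runs one way: it makes RFS look better. There is no control arm in which the same error would cancel, and RFS is part of the evidence meant to show that stereotactic radiotherapy could be a third option beside brachytherapy and IMRT.

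**Working it through.** The protocol states no RFS figure to reproduce, and its sample-size calculations concern toxicity and local control. The check is one of dates.

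**Inputs**
- Inclusion to first fraction: 1 to 28 days (Table 1, J-28 to J-1).
- First to last fraction: 10 to 12 days (VIII.2.2 gives 11-13 days; with the first fraction on day 1, the last is on day 11 to 13, which agrees with J12±1 in Table 1).
- Visit window: ±10 days (VI.5.2).

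**Offset of the 24-month scan from the second anniversary of inclusion**

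Offset = (inclusion to first fraction) + (first to last fraction) + (deviation within the window).

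| Anchor for visits | Nominal date | With the ±10-day window |
|---|---|---|
| End of radiotherapy (VI.5.2, VI.7.1) | 1 + 10 = +11 to 28 + 12 = +40 days | 11 - 10 = +1 to 40 + 10 = +50 days |
| Start of radiotherapy (Table 1 header) | +1 to +28 days | 1 - 10 = -9 to 28 + 10 = +38 days |

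Enumerating four years of start dates on the end-of-radiotherapy anchor gave 368,172 combinations. None fell before the anniversary and 11 fell on it. The extremes were 0 and +51 days, because a leap day can move either end by one day. Inclusion on the same day as the first fraction would also bring the lower limit to 0.

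On the Table 1 anchor, a scan falls on or before the anniversary only if inclusion was at most 10 days before the first fraction and the visit was early by at least as many days. If inclusion days 1 to 28 and deviations -10 to +10 were equally likely (an assumption), that is 10 + 9 + ... + 1 = 55 of 28 × 21 = 588 combinations, or 9%.

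**Which events are affected**
- First found at the 24-month assessment: dated at the scan or a later biopsy, so usually after the 2-year point. Lost from the rate.
- Found at a 3-monthly examination up to 21 months, or by imaging prompted by clinical doubt (VI.7.1): dated when found, so counted if that is within two years of inclusion.
- The last systematic scan sure to fall inside the two years is the 12-month one.

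**Illustrative size.** The documents give neither an RFS rate nor the share of recurrences detected only by the scheduled scan. Assume a constant hazard, a 2-year event risk *r*, and a share *f* of month 12-24 events found only at the 24-month scan.

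Events in months 12-24 = √(1 - r) - (1 - r); overstatement of the 2-year rate = f × that quantity.

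| r | Events in months 12-24 | f = 10% | f = 25% | f = 50% |
|---|---|---|---|---|
| 10% | 4.9% | 0.5 points | 1.2 points | 2.4 points |
| 20% | 9.4% | 0.9 points | 2.4 points | 4.7 points |
| 30% | 13.7% | 1.4 points | 3.4 points | 6.8 points |

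The range is about 0.5 to 7 percentage points, or 0.4 to 6 of 90 patients.

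**The case against.** The best defence is that the protocol never says the curve is cut at exactly two calendar years from inclusion. Landmarks and visit windows are commonly settled in an analysis plan, and one is promised before the database is frozen. The event dates are all collected, so the rate can be read wherever the analyst chooses. This limits the consequence but does not remove the point. The protocol itself fixes the origin, the visit anchor and the dating rules, and a 2-year rate computed from them omits these events unless another rule is added.

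Four stronger readings are tempting, and the documents do not support them.
- **A reader might infer that every 24-month scan is late.** That follows from the visit text, but under the Table 1 header a minority could fall on or before the anniversary.
- **A reader might infer that imaging contributes nothing after 12 months.** That is true only of systematic imaging. VI.7.1 also provides imaging on clinical doubt, and those recurrences keep their earlier dates. For the same reason, recurrences arising in the last three months cannot all be treated as missed.
- **A reader might infer that RFS contradicts the local control result.** Local and locoregional control have no stated time origin, so a conflict with the 72/83 rule in IX.1 is possible but cannot be shown.
- **A reader might infer that RFS should start at the end of radiotherapy.** That fits poorly with the intention-to-treat analysis in IX.3. The origin is undefined for included patients who never start, and events before the last fraction would have negative times; V.3.2 itself foresees stopping treatment for progression.

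**Conclusion.** The point stands in a bounded form. On the visit text, an on-schedule 24-month scan falls about 1 to 50 days after two years from inclusion. On the Table 1 header the range is -9 to +38 days, and most scans are still late. A Kaplan-Meier rate read at two years from inclusion therefore omits most recurrences first detected at that assessment and is biased upward.

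The direction and the dates rest on the protocol alone. The size of about 0.5 to 7 points rests on the assumed event risk, detection share and constant hazard. RFS is a secondary endpoint without a threshold or test, and the stated acceptance rules concern toxicity and local control, so the impact is moderate. It is still worth correcting.

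**What to change.** Keep inclusion as the origin of RFS. In IV.2 and VI.7.4, define the 2-year rate to include events found at, or triggered by, the 24-month assessment, in one of two ways:

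1. Assign both outcomes of that assessment, recurrence (including biopsies it prompts) and event-free status, to nominal 24 months, with events ordered before censorings at that time.
2. Read the curve at a landmark past the visit window: at least 24 months + 50 days from inclusion, plus a short allowance for prompted biopsies. Patients found event-free at the assessment must then be carried as event-free to the landmark. VI.7.4 censors them at their last visit, so otherwise the risk set would empty during the window and late-window events would be divided by a handful of patients.

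The first option is simpler because it treats events and event-free patients alike.

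State the same rule and a time origin for local control (the 72/83 count) and locoregional control. Reconcile the anchor in the Table 1 header with VI.5.2 and VI.7.1. Overall survival needs no change.

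The cost is a change of definition and a dating rule, with no new data, visits or patients. The reported 2-year RFS becomes slightly less favourable.
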